### Statistical analysis

Descriptive statistics will be used to report baseline patient and surgical variables. Baseline patient and procedure characteristics and perioperative outcome parameters are categorical, continuous and dichotomous variables, and will be presented accordingly. The chi-squared or Fisher’s exact test will be used to analyse the differences between the proportion of patients with recurrence.

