### Randomization

Randomization of consented study participants to either handsewn (end-to-end or Kono-S) or stapled side-to-side anastomosis will be done using an online-based system for allocation concealment (Castor EDC). Allocation concealment will be ensured, as the service will not release the randomization code until the patient has signed for informed consent and has been recruited into the trial. Randomization will be stratified for primary or repeated ileocolic resection. The randomization block sizes will not be disclosed, to ensure concealment. There is no blinding of treatment allocation for the treating surgeon. The treatment will be blinded for all other physicians (for example, gastroenterologists, central readers) and patients. A statistician blinded to treatment allocation will analyse the data.

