#### Primary endpoint

Differences in endoscopic recurrence at 6 months between the handsewn and stapled anastomosis groups will be analysed using logistic regression, which will be corrected for stratification factors and other potential confounders. Univariate associations with the risk of recurrence will be assessed using a Cox proportional hazards model, results will be reported as a hazard ratio (HR) and 95% confidence interval (CI).

Multiple variable models will be considered in the same way depending on the number of recurrences identified. The two-sided alpha-level will be set at 0.05 for statistical significance.

Differences in QoL will be analysed using mixed-model analysis of variance for repeated measures.

At the time of analysis, the most recent version of the statistical program IBM SPSS Statistics for Windows, Armonk, NY: IBM Corp. will be used.

The statistical analysis plan will be finalized before the data is locked for analysis. Decisions will be made regarding planned subgroup analyses and how to address protocol violations and any potential baseline imbalances.

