## Discussion

Surgery for Crohn’s disease has been performed since the discovery of Crohn’s disease by Burrill Crohn in 1932 [25]. It is remarkable that, even after 90 years of surgical advancements, we still do not know the preferred anastomosis technique after ileocolic resection concerning safety, diagnosis of Crohn’s disease recurrence, functional outcome, and costs. The proposed trials aim to answer this unmet need.

The primary endpoint of the present study is postoperative endoscopic recurrence after 6 months. This is a crucial endpoint, because the diagnosis of endoscopic recurrence signifies disease recurrence. Disease recurrence typically necessitates the resumption of medical therapy which is in general long-term immunosuppressive or biological therapy. This entails a sequence of biological treatments for as long as the clinical symptoms do not require another surgical intervention. On the contrary, clinical recurrence has been the primary outcome in many studies in the postoperative setting, but its definition remains debated. Most importantly, there does not seem to be a strong correlation between clinical recurrence and endoscopic recurrence [26]. Furthermore, functional disorders resulting from ileocolic resection might interfere with symptoms indicating clinical recurrence.

According to ECCO guidelines, it is recommended to initiate medical therapy after surgery if the patient has one risk factor for recurrence (smoker, prior intestinal surgery, penetrating disease, perianal disease, granulomas or myenteric plexitis) [27]. All other patients should undergo endoscopy within 6–12 months to assess endoscopic recurrence. Notably, assessment of endoscopic recurrence has shown a high degree of variability (10–70%) with significant implications for both patients and society (diagnosis of recurrence and starting expensive medication) [28, 29].

The Rutgeerts score has been developed to classify endoscopic recurrence with a score of ≥2 indicating its presence. The modified Rutgeerts classification was introduced to differentiate between patients with ulcerations solely at the anastomotic line (2a) and those with ulcerations extending into the neoterminal ileum (2b). Nevertheless, endoscopic scoring remains highly variable, probably due to observer bias as evident from the significant variability between local and central readings [30].

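### Only the handsewn-versus-stapled endoscopic comparison is adjusted for the stratification factor; end-to-end versus Kono-S and the secondary recurrence outcomes are left with a general unadjusted test, at a small cost in power

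*Protocol article*

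**What the plan says.** Four statements in the protocol article bear on this point.

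- Randomization section: "Randomization will be stratified for primary or repeated ileocolic resection". The sentence follows a description of allocation in these terms: "Randomization of consented study participants to either handsewn (end-to-end or Kono-S) or stapled side-to-side anastomosis will be done using an online-based system". How patients are allocated between the two handsewn techniques is not described separately.
- Discussion: the guideline risk factors for recurrence are listed as "smoker, prior intestinal surgery, penetrating disease, perianal disease, granulomas or myenteric plexitis". Prior intestinal surgery is in essence the stratification factor. No effect size is given.
- Statistical analysis, Primary endpoint: "Differences in endoscopic recurrence at 6 months between the handsewn and stapled anastomosis groups will be analysed using logistic regression". The comparison and the outcome are both named. The adjustment is attached to this model alone: "which will be corrected for stratification factors and other potential confounders". A later sentence leaves room for more: "Multiple variable models will be considered in the same way depending on the number of recurrences identified".
- Statistical analysis, opening paragraph: "The chi-squared or Fisher’s exact test will be used to analyse the differences between the proportion of patients with recurrence". No comparison, phase or type of recurrence is named.

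The outcomes section lists 6-month histologic and clinical recurrence as secondary outcomes. The sample size section plans phase two on end-to-end versus Kono-S, 28% versus 13%.

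**The concern.** The protocol accepts that the primary comparison should be adjusted for the stratification factor, but does not carry this over to the other recurrence comparisons. On the text shown, the general unadjusted test is the only test of proportions that reaches them. If handsewn proves superior, end-to-end versus Kono-S becomes the trial's final question.

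When a prognostic factor is balanced between arms by design, an unadjusted test still counts the variation between strata as noise. Its true type I error then falls below the nominal level, and some power is given up. The question is how much.

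**Working it through.** **1. Reproduce the plan's phase-two size (Netherlands).** Inputs from the sample size section: 28% versus 13%, two-sided alpha 0.05, and 80% power (stated for Dutch phase one). The difference is d = 0.15 and the mean rate is 0.205.

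n = [1.960 × √(2 × 0.205 × 0.795) + 0.842 × √(0.28 × 0.72 + 0.13 × 0.87)]² / 0.15² = (1.119 + 0.472)² / 0.0225 = 112.5, so 113 per arm.

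Inflated for 10% dropout: 113 / 0.9 = 125.6, so 126. With continuity correction and no dropout: (112.5 / 4) × [1 + √(1 + 4 / (112.5 × 0.15))]² = 125.5, also 126. The protocol has 55 + 71 = 126 per handsewn arm. The figure therefore reproduces for an unadjusted two-proportion test.

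**2. Evaluable numbers.** Carrying the 10% dropout over to phase two (an assumption), the Netherlands has 126 × 0.9 ≈ 113 per arm. In Italy the stated total of 277 gives 63 + 88/2 = 107 per arm, and 107 × 0.9 ≈ 96.

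**3. Conservatism of the crude test, by formula.** Assumptions not in the protocol: 30% repeat resections, and a repeat-versus-primary odds ratio (OR) of 1.5 to 4. With exact balance within strata, the crude variance is too large by the between-stratum share

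s = f(1 − f)(r₂ − r₁)² / [p(1 − p)],

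where f is the repeat share, r₁ and r₂ are the stratum risks and p is the overall risk. The effective critical value is 1.960 / √(1 − s). At OR 3 and p = 0.205, r₁ = 0.147 and r₂ = 0.341 (check: 0.7 × 0.147 + 0.3 × 0.341 = 0.205). Then s = 0.21 × 0.194² / 0.163 = 0.048, the critical value is 2.009 and the true alpha is about 0.044.

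**4. Simulation with the same assumptions.** 400,000 runs per setting; Pearson chi-squared against Mantel-Haenszel; power at 28% versus 13%.

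| OR | Crude alpha, 113 / 96 per arm | Power at 113: crude, stratified (gain) | Power at 96: crude, stratified (gain) |
|---|---|---|---|
| 1.5 | 0.049 / 0.050 | 80.9%, 81.0% (0.1) | 74.4%, 74.5% (0.1) |
| 2 | 0.047 / 0.048 | 81.1%, 81.5% (0.4) | 74.6%, 75.0% (0.4) |
| 3 | 0.044 / 0.045 | 81.5%, 82.6% (1.2) | 74.9%, 76.1% (1.2) |
| 4 | 0.041 / 0.041 | 81.7%, 83.6% (1.9) | 75.3%, 77.6% (2.2) |

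Gains are in percentage points, computed before rounding. The stratified test holds alpha at about 0.05 throughout. Varying the repeat share from 20% to 40% with all patients evaluable (126 or 107 per arm) gives the same picture: at most 1.3 points up to OR 3, and 2.3 to 2.8 points at OR 5.

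**5. If the end-to-end/Kono-S allocation is not stratified.** The crude alpha is then about nominal. Adjustment still gains about 0.2 to 2.8 points over OR 2 to 4, because it removes chance imbalance and between-stratum noise.

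**6. Fisher, without any strata (exact enumeration).** At 113 per arm the type I error is about 0.035 and power 76.4%, against 80.8% for chi-squared. At 126 per arm power is 81.0% against 84.7%. This loss comes from the discreteness of Fisher's test and would be there without stratification.

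**The case against.** The strongest reply is that no sentence assigns the crude test to phase two or to the secondary outcomes. The sentence is general and stands beside the descriptive statistics. Multivariable models are left open, and the analysis plan is to be finalised before data lock. This stands in part: the reach of the crude test is an inference. But the protocol does state a test for recurrence proportions, and it limits the adjusted model to one named comparison. The matters it expressly defers are subgroups, protocol violations and baseline imbalances, and the sentence on multivariable models commits to nothing.

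Stronger readings are tempting, and the documents do not support them:

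- A reader might infer that phase two is underpowered because of the crude test. Dutch phase two was sized for an unadjusted test and keeps about 81% power with chi-squared after 10% dropout. The lower Italian power follows from the stated total; stratifying raises it only to about 75% to 78%.
- A reader might charge the whole gap between Fisher and a stratified test to ignoring the strata. Most of it is Fisher's own conservatism. With about 0.205 × 113 ≈ 23 events expected per arm, chi-squared would ordinarily be used.
- A reader might conclude that the phase-two error rate is certainly too low. That requires balance within strata between the two handsewn techniques, which the Randomization section does not describe.
- A reader might suspect that pooling patients from both phases biases the comparison. The planned handsewn arms are equal in phase one, and the Dutch extension adds 71 per group. With equal allocation in both phases, technique is not confounded with phase. A phase covariate is good practice, but its benefit has not been quantified here.

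The stratum effect may also be weaker than assumed. Patients with a risk factor may receive prophylaxis under the guidelines the protocol cites, and below OR 2 the loss nearly vanishes.

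**Conclusion.** The point holds as a modest matter of efficiency and consistency. Stratum adjustment is stated for one recurrence comparison, and the only test of proportions that reaches the others is unadjusted. That test is valid and errs, if at all, on the conservative side: true alpha is about 0.041 to 0.050 for stratum odds ratios from 4 down to 1.5. Relative to chi-squared, the power given up is about 0 to 0.5 points at an odds ratio of 1.5 to 2, about 1 at 3 and about 2 at 4. These figures rest on an assumed 30% of repeat resections, 10% dropout in phase two and, for the alpha values, balance within strata. The protocol gives neither the repeat share nor the odds ratio. The calculation covers the phase-two endoscopic comparison. For histologic and clinical recurrence the protocol gives no rates, so only the direction is claimed.

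**What to change.** Extend the existing model in the Statistical analysis section, for example: end-to-end versus Kono-S in phase two, and the comparisons of histologic and clinical recurrence, are analysed by the logistic regression used for the primary endpoint, adjusted for primary or repeat resection and, in phase two, also for trial phase; a stratified Mantel-Haenszel or exact test is used if events are sparse. Keep chi-squared and Fisher for descriptive tables. It would also help to say whether allocation between end-to-end and Kono-S is stratified.

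The cost is a sentence or two in the protocol or the analysis plan, written before data lock. The stratum is needed for randomisation and so is already recorded, and trial phase follows from the enrolment date. No extra patients or data are required.

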#### Primary endpoint

Differences in endoscopic recurrence at 6 months between the handsewn and stapled anastomosis groups will be analysed using logistic regression, which will be corrected for stratification factors and other potential confounders. Univariate associations with the risk of recurrence will be assessed using a Cox proportional hazards model, results will be reported as a hazard ratio (HR) and 95% confidence interval (CI).

Multiple variable models will be considered in the same way depending on the number of recurrences identified. The two-sided alpha-level will be set at 0.05 for statistical significance.

Differences in QoL will be analysed using mixed-model analysis of variance for repeated measures.

At the time of analysis, the most recent version of the statistical program IBM SPSS Statistics for Windows, Armonk, NY: IBM Corp. will be used.

The statistical analysis plan will be finalized before the data is locked for analysis. Decisions will be made regarding planned subgroup analyses and how to address protocol violations and any potential baseline imbalances.

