##### Assessment of primary endpoint (endoscopic recurrence)

All patients will undergo endoscopy with biopsies taken from the distal ileum and proximal colon on either side of the anastomosis to assess endoscopic and histologic recurrence at 6 months after surgery. Endoscopic results will be classified according to the SES-CD subdivided according to location and the (modified) Rutgeerts scoring system [24]. All colonoscopies must be video recorded according to a standard operational procedure (video). The quality of endoscopic scoring and over scoring will be assessed comparing the scoring of the local gastroenterologist with that of the central reading panel.

After endoscopic assessment at 6 months, medication can be initiated according to the severity of endoscopic recurrence according to the guidelines and the treating physician’s preference.

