### Primary and secondary outcomes

The primary outcome is endoscopic recurrence at 6 months following ileocolic resection, defined as Rutgeerts score ≥ i2b assessed by local and central reading separately and blinded for the type of anastomosis. The quality of endoscopic scoring and over scoring will be assessed comparing the local scoring by the treating gastroenterologist with the central reading scoring for the different types of anastomosis.

Secondary outcomes include postoperative morbidity, the 6 months histologic and clinical recurrence rate and the need of restarting immunosuppressive medication within the first year postoperatively for endoscopic or clinical recurrence. For long term results, patient will be followed for at least 5 years to determine reoperation rate for recurrent disease at the anastomotic site. Additionally, quality of life will be measured with IBDQ, EQ-5D and SF- 36 together with health care consumption and costs.

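### The Primary endpoint section prescribes Cox hazard ratios for associations with recurrence, although endoscopic recurrence is a yes/no status read at one scheduled 6-month endoscopy and has no event time

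*Protocol article*

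**What the plan says.** All places are in the protocol article.

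- Primary and secondary outcomes: "The primary outcome is endoscopic recurrence at 6 months following ileocolic resection", defined as a Rutgeerts score of i2b or worse.
- Assessment of primary endpoint (endoscopic recurrence): all patients have an endoscopy with biopsies "to assess endoscopic and histologic recurrence at 6 months after surgery". No other scheduled endoscopy is described.
- Sample size calculation: both studies are sized on 50% versus 25% with a continuity-corrected test of proportions.
- Statistical analysis: "The chi-squared or Fisher’s exact test will be used to analyse the differences between the proportion of patients with recurrence".
- Primary endpoint, first sentence: "Differences in endoscopic recurrence at 6 months between the handsewn and stapled anastomosis groups will be analysed using logistic regression". The model is to adjust for the stratification factors and for further confounders that are not named.
- Primary endpoint, next sentence: "Univariate associations with the risk of recurrence will be assessed using a Cox proportional hazards model", with results given as hazard ratios and 95% confidence intervals. The following paragraph adds: "Multiple variable models will be considered in the same way depending on the number of recurrences identified".

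No event date, censoring rule or time-to-recurrence outcome is defined for endoscopic recurrence. A time-based outcome does exist elsewhere: reoperation for recurrent disease at the anastomotic site, followed for 5 years (Assessment of surgical recurrence).

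**The concern.** A Cox model needs the time at which each event happened. A single planned endoscopy shows whether recurrence is present; it does not show when it began. An analyst who follows the Cox sentence must therefore supply a time, and there are two candidates.

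- Every patient is given 6 months. All events are then tied, and the result depends on how the software treats ties.
- The endoscopy date is used. The model then treats the appointment date as the moment of recurrence, so differences in scheduling enter the hazard ratio.

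Either way the hazard ratio does not describe how fast recurrence develops. The risk-factor results, univariable and multivariable, would be reported on a scale that cannot be interpreted. They would also not be comparable with the odds ratio from the logistic model for the treatment effect on the same outcome.

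**Working it through.** **1. The design treats the endpoint as a proportion.** Inputs from Sample size calculation, End2End: p1 = 0.50, p2 = 0.25, ratio r = 2, two-sided alpha 0.05, power 80%, continuity correction, 10% dropout.

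- Weighted mean proportion = (0.50 + 2 × 0.25)/3 = 1/3.
- n = [1.96 × √(3 × 1/3 × 2/3) + 0.8416 × √(2 × 0.25 + 0.1875)]² / (2 × 0.25²) = (1.600 + 0.698)² / 0.125 = 42.25.
- With continuity correction: (42.25/4) × [1 + √(1 + 6/(42.25 × 2 × 0.25))]² = 48.1, so 49 stapled and 98 handsewn, 147 in total.
- 147/0.9 = 163.3, so 164, against 165 stated.

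The stated figure is reproduced to within rounding. No hazard ratio or event count enters.

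**2. An example table at the design point.** End2End enrols 55 stapled and 110 handsewn; after 10% dropout about 49 and 99 are evaluable. At 50% and 25% this is about 25/49 and 25/99 with recurrence. Arm is used as the covariate only because the documents give rates for it; any binary risk factor with these counts gives the same results.

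**3. Cox with all times equal, Breslow ties.** The log partial likelihood is 25β − 50 log(99 + 49e^β).

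- Setting its derivative to zero gives e^β = (25/49)/(25/99) = 2.02, which is the risk ratio.
- The information is 50 × 0.5 × 0.5 = 12.5, so SE = 1/√12.5 = 0.283, which equals √(1/25 + 1/25).
- z = ln(2.02)/0.283 = 0.703/0.283 = 2.49, p = 0.013.
- The correct SE of a log risk ratio is √(1/25 − 1/49 + 1/25 − 1/99) = 0.222. The Breslow SE is 0.283/0.222 = 1.27 times as large.

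**4. Same data, other methods.**

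| Method | Estimate | p |
|---|---|---|
| Cox, Breslow ties | HR 2.02 | 0.013 |
| Cox, Efron ties | HR 2.40 | 0.002 |
| Logistic regression | OR (25 × 74)/(24 × 25) = 3.08 | 0.002 |
| Chi-squared, uncorrected | – | 0.002 |

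The logistic p-value follows from SE = √(1/25 + 1/24 + 1/25 + 1/74) = 0.368 and z = 1.126/0.368 = 3.06. The two hazard ratios differ only through the tie option.

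**5. A borderline table, 25/50 versus 33/100.** Breslow: ln(1.515)/√(1/25 + 1/33) = 0.4155/0.2651 = 1.57, p = 0.117. Logistic p = 0.045; chi-squared p = 0.044; Fisher p = 0.052.

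**6. Cox on endoscopy dates.** The documents give no spread of dates, so this rests on assumptions: SD 0.5 month, 40% recurrence in both groups, 50 and 100 evaluable, 1,000 simulated runs. If both groups are scoped at the same average time, Cox rejects in 4% of runs and logistic in 4%. If one group is scoped 0.5 month earlier on average, Cox rejects in 91% and logistic in 5%. The shift is an illustration; nothing in the documents says that it will occur.

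**The case against.** The strongest reply is that the sentence immediately before the Cox sentence already gives the treatment contrast to logistic regression, adjusted for the stratification factor, and that the Cox sentence is about risk-factor screening. This stands. A reader might infer that the primary effect size and p-value hang on an arbitrary choice among three methods. The documents do not support that.

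A reader might also infer a loss of power. In simulation, Cox with Breslow ties has 73% power against 86% for chi-squared with 49 and 99 evaluable patients, and about 80% against 90% with 57 and 113; its type I error is about 1.5%. These figures need three conditions together: Cox as the deciding arm comparison, every time tied, and Breslow ties. The text prescribes none of them expressly. With Efron ties the example p-value is the same as the logistic one to three decimals, and the Breslow error is conservative.

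The chi-squared/Fisher sentence is not a serious conflict. These are tests, not a further effect measure; chi-squared agrees closely with logistic regression, and Fisher parts from it only near the threshold. The sentence may also serve crude comparisons or the histologic and clinical recurrence outcomes. Ranking supportive tests and naming covariates can be left to the analysis plan. Endoscopy brought forward because of symptoms would distort a date-based hazard ratio, but the documents do not describe it.

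Finally, the Cox sentence may be misplaced and meant for reoperation. It says recurrence without the word endoscopic, and the section also covers quality of life and software. That is possible, but the sentence stands under Primary endpoint, directly after the 6-month endoscopic comparison, and does not mention reoperation. If that was the intent, the wording still needs correcting. This is also not an omission to be left to the analysis plan: the article positively names a method that does not fit.

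**Conclusion.** The point holds, limited to the Cox sentence and the multivariable models tied to it. For a status read once at a scheduled visit, a hazard ratio is the wrong measure. In the example its value moves from 2.02 to 2.40, and its p-value from 0.013 to 0.002, on tie handling alone, with a Breslow standard error about 27% too large for a log risk ratio. These figures assume recurrence at the design rates, the evaluable numbers left after 10% dropout, and all times set equal.

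On the text as it stands, the confirmatory comparison is the adjusted logistic regression, and it and the stated power are intact. They would be affected only if Cox were applied to the arm contrast, which the section neither says nor expressly rules out. Because a finding of handsewn superiority opens phase two, that is worth settling in one sentence.

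**What to change.** Four changes of wording in the Statistical analysis and Primary endpoint sections, to be made before data lock:

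1. Replace the Cox model with univariable and multivariable logistic regression for all associations with 6-month endoscopic recurrence. Report odds ratios with 95% confidence intervals; risk ratios or risk differences are equally acceptable.
2. State that the logistic model adjusted for the stratification factor (primary or repeated resection) decides the primary handsewn-versus-stapled comparison.
3. Label the chi-squared or Fisher's exact test as unadjusted support.
4. If a Cox model is wanted, assign it by name to time to reoperation in the 5-year follow-up.

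The sample size does not change, because it already rests on proportions. No extra data are needed.
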